#### 5.1.2 Adverse Events Definition and Reporting

All patients will be provided with the contact information of the Principal Investigator if they feel that they have been adversely affected by participating in the surveys or in the in-person or video-based PFMT sessions.

This protocol presents minimal risks to the subjects and Unanticipated Problems Involving Risks to Subjects or Others (UPIRSOs), including adverse events, are not anticipated. In the unlikely event that such events occur, Reportable Events (which are events that are serious or life-threatening and unanticipated (or anticipated but occurring with a greater frequency than expected) and possibly, probably, or definitely related) or Unanticipated Problems Involving Risks to Subjects or Others that may require a temporary or permanent interruption of study activities will be reported immediately (if possible), followed by a written report within 5 calendar days of the Principal Investigator becoming aware of the event to the IRB (using the appropriate forms from the website) and any appropriate funding and regulatory agencies. The investigator will apprise fellow investigators and study personnel of all UPIRSOs and adverse events that occur during the conduct of this research project through weekly lab meetings to survey the progress of the study. The protocol's research monitor(s), e.g., Data and Safety Monitoring Boards, study sponsors, funding and regulatory agencies, and regulatory and decision-making bodies will be informed of physical harm adverse events within 5 days of the event becoming known to the principal investigator.

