| Study Date Range and Duration
December 2024 – August 2026                                                                                                                                                                                                                                                                                                                  |
| Number of Study Sites
Yale New Haven Hospital                                                                                                                                                                                                                                                                                                                              |
| Primary Outcome Variables
We will use direct patient evaluation by pelvic floor therapists, a validated system usability survey to evaluate the ease of use of the web-based platform containing PFMT videos and monitor for adverse events.                                                                                                                               |
| Secondary and Exploratory Outcome Variables (if applicable)
Short Form 12 score, Cleveland Clinic Incontinence Score (CCIS), Patient Assessment of Constipation Symptoms (PAC-SYM), International Consultation on Incontinence Questionnaire Short Form (ICIQ-SF), and Pelvic Organ Prolapse Symptom Score (POP-SS) to assess improvement in symptoms and quality of life. |
| Study Population
Study population will include patients who have an indication for referral for pelvic floor rehabilitation (PFR).                                                                                                                                                                                                                                         |
| Number of Participants                                                                                                                                                                                                                                                                                                                                                        |

We plan to enroll 10-20 patients. This is a pilot study aimed at assessing feasibility, so this sample size is similar to other feasibility trials.

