## 2.2 Purpose of Study/Potential Impact

Evaluating the feasibility and safety of video-based PFMT will allow us to determine if this video-based training could be offered as a treatment alternative for patients with pelvic floor dysfunction.

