**Pelvic Floor Muscle Therapy Sessions (video-based):**

Practicing PFMT using the video-based application may similarly be time consuming and uncomfortable for patients to perform. Additionally, as patients will be performing these exercises alone without supervision, there is the risk of harm to self. There is no guarantee that the instruction and exercises in these sessions will prevent patients from having persistent or worsening pelvic floor dysfunction as they are opting out of standard of care visits. Patients can choose to opt out of certain exercises if desired.

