## 4.2 Outcome Variables

### 4.2.1 Primary Outcome Variables

SUS, percentage of video completion, change in the graded evaluation of exercises by pelvic floor therapist pre and post intervention, adverse events

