#### 5.1.1 Data Collection

The survey information will be collected by a trained survey either in person or filled out independently by the study participant using a Yale-licensed Qualtrics platform. If there are technical difficulties, a paper-based version of the assessment tool will be substituted and later inputted. This data and the clinical data will be collected from the electronic medical records (e.g., Epic® chart reviews) and will be securely stored in the HIPAA compliant RedCap database. The assessment by the pelvic floor therapist will also be secured inputted into the RedCap database.

At the completion of the study period, we will compare the assessment of PFMT adequacy as assessed by the pelvic floor therapists, usability of the video-based application, and any adverse events as our primary outcome for feasibility and safety. We will analyze the change in the SF-12 score, CCIS, PAC-SYM, pre and post intervention to evaluate any change as our secondary outcome evaluating for efficacy of video-based PFMT.

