### 5.3.3 Study Visits (is applicable)

1. Initial clinic visit
  - a. SF-12
  - b. And one of the following surveys:
    - i. CCIS
    - ii. PAC-SYM
    - iii. ICIQ-SF
    - iv. POP-SS
2. In person visit with pelvic floor therapist (1 hour)
  - a. Introduction to PFMT clinical visit by a certified pelvic floor therapist
  - b. Graded evaluation of pelvic floor exercises on a scale of 1-3 ( 1= cannot replicate in any meaningful way, 2 = partially, 3 = fully perform)
3. Midway check-in with research team member (15 minutes)
  - a. Elicit feedback on self-direct video-based training
  - b. Completion of SUS
4. Completion in person visit clinical visit with pelvic floor therapist (1 hour)
  - a. Graded evaluation of pelvic floor exercises on a scale of 1-3 (1= cannot replicate in any meaningful way, 2 = partially, 3 = fully perform)
5. Completion survey within 1 week of seeing pelvic floor therapist
  - a. SF-12
  - b. And one of the following surveys:
    - i. CCIS
    - ii. PAC-SYM
    - iii. ICIQ-SF
    - iv. POP-SS
  - c. SUS

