### 5.4.3 Planned Analyses

The primary analysis to evaluate for feasibility and safety will involve the percentage of patients who successfully learned PFMT, analysis of incidence of adverse events and overall score of usability for the web-based videos. We will also evaluate the ability of participants to successfully complete the exercises based on the graded scoring by the pelvic floor therapists. Analysis of secondary outcomes

related to symptom improvement and quality of life will analyze SF-12, CCIS, PAC-SYM, ICIQ-SF and POP-SS scores.

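### Adverse-event incidence is part of the primary analysis, but the only capture route specified is patient-initiated contact, so it is liable to be under-counted

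*Protocol*

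**What the plan says.** Adverse events are a primary outcome throughout the protocol. Section 4.2.1 lists "SUS, percentage of video completion, change in the graded evaluation of exercises by pelvic floor therapist pre and post intervention, adverse events". Section 5.1.1 takes "any adverse events as our primary outcome for feasibility and safety", and the primary analysis in 5.4.3 includes "analysis of incidence of adverse events and overall score of usability for the web-based videos".

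On how events become known, section 5.1.2 says: "All patients will be provided with the contact information of the Principal Investigator if they feel that they have been adversely affected". The rest of that section defines reportable events and deals with onward reporting once the investigator is aware of one. The Synopsis adds "videos and monitor for adverse events" but gives no method, timing or instrument.

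Section 2.3.1 describes the setting: "as patients will be performing these exercises alone without supervision, there is the risk of harm to self".

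The scheduled contacts are set out in 4.1.1, 5.2 and 5.3.3. At the week-4 check-in the team is to "Elicit feedback on self-direct video-based training" and collect the SUS. The final therapist visit carries the 1-3 exercise grading. The completion survey consists of the SF-12, one symptom scale and the SUS.

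Section 5.4.6 excludes patients who complete under 75% of the videos or who miss the initial or final therapist visit. It sets no separate population for safety.

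**The concern.** An incidence needs a numerator sought in the same way from everyone in the denominator. Here the numerator depends on a patient deciding that something was an adverse effect of the study and then making contact. Milder events, and events the patient does not link to the exercises, are the ones most easily lost. This matters more in an eight-week home programme in which no therapist is watching.

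The expected direction of error is downward. A count of zero could mean that nothing happened or that nobody reported it, and the data could not tell the two apart. The exclusion in 5.4.6 pushes the same way: a patient who gives up the videos or skips the final visit because of an event may leave the analysis together with that event.

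Safety also feeds a stated use of the results. Section 2.2 says that evaluating feasibility and safety "will allow us to determine if this video-based training could be offered as a treatment alternative".

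**Working it through.** **No figure to reproduce.** The protocol gives no expected event rate, and section 5.4.2 takes its 10-20 patients from prior feasibility studies. The check is therefore a reading of every contact, followed by an illustration on stated assumptions.

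**Where could an event be picked up?**

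| Source | Section | Listed content | Adverse-event question listed? |
|---|---|---|---|
| Investigator contact details | 5.1.2 | Patient makes contact | Patient-initiated only |
| Week-4 check-in | 4.1.1, 5.2, 5.3.3 | Feedback, SUS | No |
| Final therapist visit | 4.1.1, 5.2, 5.3.3 | 1-3 exercise grading | No |
| Completion survey | 4.1.1, 5.3.3 | SF-12, one symptom scale, SUS | No |
| Record review | 2.3.1, 5.1.1, Subject Confidentiality | Demographics, unspecified clinical data, medical and surgical history | No |
| Synopsis monitoring statement | Synopsis | No method given | No |

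**What incomplete capture does to the count.** Inputs:
- n = 10 and n = 20, the limits in 4.3.1.
- p, the true risk per patient of an event: assumed 10%, with 20% and 30% as a range.
- c, the fraction of affected patients whose event is recorded: assumed 100%, 50% and 30%.

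Chance that no event is recorded = (1 − p × c)^n.

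At p = 10%:
- c = 100%: 0.90^20 = 12%; 0.90^10 = 35%.
- c = 50%: 0.95^20 = 36%; 0.95^10 = 60%.
- c = 30%: 0.97^20 = 54%; 0.97^10 = 74%.

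At p = 20%:
- c = 100%: 0.80^20 = 1.2%; 0.80^10 = 10.7%.
- c = 50%: 0.90^20 = 12%; 0.90^10 = 35%.
- c = 30%: 0.94^20 = 29%; 0.94^10 = 54%.

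At p = 30%:
- c = 100%: 0.70^20 = 0.1%; 0.70^10 = 2.8%.
- c = 50%: 0.85^20 = 3.9%; 0.85^10 = 19.7%.
- c = 30%: 0.91^20 = 15%; 0.91^10 = 39%.

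**What the 5.4.6 exclusion can do.** Suppose one of 20 patients has an event and stops because of it. Counted over everyone who started, the result is 1/20 = 5%. With that patient excluded it is 0/19 = 0%.

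**What zero events can show with complete capture.** The exact two-sided 95% upper limit for 0/n is 1 − 0.025^(1/n):
- n = 20: 1 − 0.025^(1/20) = 16.8%.
- n = 10: 1 − 0.025^(1/10) = 30.8%.

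These limits apply to the true event rate only if every patient was asked. With partial capture they bound the rate of recorded events, which is lower.

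**The case against.** The strongest reply is that patients are not out of sight. A team member contacts each of them at week 4 to hear feedback and check progress, a pelvic floor therapist spends an hour with them at the end, and clinical data are taken from the record. Worsening on the chosen bladder, bowel or prolapse scale would show in the pre/post scores of those who complete them. The attached surveys and any check-in script are not to hand.

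Much of this stands. A reader might infer that no event can reach the study unless the patient makes contact, or that under-counting is established. The protocol supports neither: these contacts could surface events, and only the direction of bias is expected. But none of them is assigned to adverse-event collection, the symptom scale covers one domain per patient, and those who stop are the least likely to be seen at the end.

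A reader might also infer that the protocol will declare the programme safe if no event is recorded. It contains no such rule. Section 2.2 is a general statement resting on feasibility and safety together, and 5.4.3 only lists what will be analysed. Nor does the wording in 2.3.1 refer to intentional injury; it concerns harm from exercising without supervision.

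The statistical analysis plan, which is not shown, does not answer the point. It can say how collected events are analysed, but whether each participant is asked is a study procedure and cannot be recovered afterwards.

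**Conclusion.** The point holds in this form: an outcome in the primary analysis has no systematic ascertainment specified, and its incidence is liable to be too low. The reading of sections 5.1.2, 5.2, 5.3.3 and 5.4.6 rests on the protocol alone. The size of the bias cannot be derived from it. In the illustration at an assumed 10% rate, capturing half rather than all of the events roughly triples the chance of a zero count at n=20 (12% to 36%) and raises it from 35% to 60% at n=10. At higher assumed rates a zero count is less likely, but the pattern is the same. Rates and capture fractions are assumptions, and the calculation treats patients as independent.

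This should be changed: it affects a primary outcome and is cheap to put right before data are collected.

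**What to change.** - **Sections 5.1.2, 5.2 and 5.3.3:** add a short fixed set of adverse-event questions to the week-4 check-in and to the final visit or completion survey. Put the same questions to every participant, including those who stopped the videos or missed the final visit. Keep the investigator contact details as an additional route. The fixed set also settles what is counted as an event.
- **Sections 5.4.3 and 5.4.6:** report adverse events as n/N with an exact 95% confidence interval over everyone who started the videos, and state that the 5.4.6 exclusion does not apply to this outcome.
- **Reporting:** if no event is recorded, give the upper limit beside the zero (16.8% for 0/20, 30.8% for 0/10).

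**Cost:** two to three minutes at each existing contact, a short REDCap form, an attempt to reach those who stopped, and an IRB amendment. No visit is added.

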## **5.2 Study Schedule**

Initial surveys completed at initial clinic visit

In person visit standard of care visit with pelvic floor therapist and graded scoring of exercise completion ability (1 hour)

8 weeks of online, video-based PFMT program; videos were created by Yale (website: <https://pelvicfloorthrapy.wixsite.com/yale-video-based-pel>)

Midway check-in with research team and completion of SUS survey (15 minutes)

Completion in person standard of care visit with pelvic floor therapist and graded scoring of exercise completion ability (1 hour)

Completion surveys after 8 weeks of video-based PFMT (within 1 week of in person visit)

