**Study Schedule**

Patients will be expected to complete a 5–10-minute survey at initial enrollment. They will have one in-person session with a pelvic floor therapist prior to starting the 8-week video-based PFMT course. They will have a midpoint check in after 4 weeks to monitor progress. Afterwards, they will have a final in person session with a pelvic floor therapist along with a final set of surveys that should take an estimated 10-15 minutes. We have also attached a figure with the study design.

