## 1.2 Prior Experience (if applicable)

Our group conducted a study on patient reported barriers to completion of in-person PFR. We found the average time between referral and attendance of the first PFR session was 10 weeks. The two major barriers to completion included delay in available sessions (24%) and travel distance for attendance (20%). Furthermore, 35% of patients stated they would be amenable to a hybrid option using either telehealth or video-based strategies and 58% of patients would attend more sessions if there was a video-based option.

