**3.3 Secondary Objective (if applicable)**

To determine whether video-based PFMT can improve symptomatology and QoL.

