## 4 Study Design

### 4.1.1 General Design Description

Patients will be enrolled during the clinic visit when they are initially referred for PFR. It will be explained that they are forgoing standard of care of all in-person pelvic floor rehabilitation and will complete the initial survey at this time. They will then have an introductory session with a pelvic floor therapist to assess their baseline function, which does not differ from the standard of care other than the pelvic floor therapist using a graded scoring system to assess exercise completion ability. This initial visit will be prioritized as the waitlist for pelvic floor rehabilitation can be up to 6 months. Then they will complete the 8 weeks of remote, self-directed video-based PFMT. At the midway point after completing 4 weeks of the remote, self-directed video based PFMT, patients will be contacted by a member of the research team to elicit feedback and complete a system usability scale to evaluate patient perspective of the online training program. After this period, they will have another in-person session with the same pelvic floor physical therapist to assess ability to complete exercises successfully with the same graded scoring system. They will then complete a system usability scale survey and repeat the initial surveys for QoL and symptom surveys within 2 weeks of the final in person pelvic floor therapist appointment.

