### **5.3.2 Recruitment, Enrollment and Retention (if applicable)**

Potential subjects will be identified by reviewing clinic patients with the provider and patients will be targeted for in-person recruitment by the treating provider with the trained research assistant present. We may contact patients of treating providers who have given written agreement to have their patients who are eligible for PFR to be contacted if unable to consent in person. The study will be introduced to the patients by the treating provider and the trained research assistant will consent and complete initial survey administration during the initial visit, or if not able will complete the survey via telephone call or electronic communication. Patients will be compensated a total of \$50 for attendance of the first and last in-person PFMT sessions.

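### The baseline SF-12 and symptom surveys are taken at referral, so the pre-post change read as video efficacy includes a pre-course wait with no upper limit

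*Protocol*

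**What the plan says.** Section 4.1.1 sets the entry point: "Patients will be enrolled during the clinic visit when they are initially referred for PFR". The first surveys are done at that same visit, and Section 5.2 repeats this: "Initial surveys completed at initial clinic visit". The procedure list in Section 5.1 and the visit list in Section 5.3.3 give the same order. Section 5.3.2 adds a fallback for patients who cannot do the survey then, "or if not able will complete the survey via telephone call or electronic communication", with no date limit and no tie to the start of the course.

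The course comes later. The Synopsis says: "They will have one in-person session with a pelvic floor therapist prior to starting the 8-week video-based PFMT course". On the wait for that session, Section 4.1.1 says: "This initial visit will be prioritized as the waitlist for pelvic floor rehabilitation can be up to 6 months". Section 1.2 reports the group's earlier experience: "We found the average time between referral and attendance of the first PFR session was 10 weeks". No maximum interval is stated for trial patients. At the first therapist visit Section 5.3.3 lists only the introduction to the therapy and the 1-3 grading of exercises; the SF-12 and symptom surveys are not repeated.

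At the other end, Section 5.3.3 has: "Completion survey within 1 week of seeing pelvic floor therapist". Section 5.2 also gives 1 week, whereas Section 4.1.1 allows 2 weeks; these need to be reconciled. In all three places the final surveys follow the final in-person session.

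The secondary objective in Section 3.3 is: "To determine whether video-based PFMT can improve symptomatology and QoL". Section 5.1.1 reads the before-and-after change as efficacy of the video programme, and Section 5.4.1 tests it with a paired t-test in a single group.

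**The concern.** A before-and-after comparison can speak to an intervention only if the first measurement sits close to its start. Here the first measurement is tied to referral and has no fixed relation to the first video. Whatever happens to symptoms and quality of life between referral and the first therapist visit enters the paired difference together with any effect of the course, and the paired test cannot separate them. The interval will also differ between patients according to how soon each gets a therapist appointment.

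Survey timing is set by the visit schedule, so an analysis plan cannot repair this afterwards: a score that was not collected at the start of the course cannot be recovered. At stake is how Hypothesis B and the secondary objective are read. The primary outcomes are not touched. The exercise grading has its baseline at the therapist visit just before the course, and the usability score, video completion and adverse events do not use the referral survey.

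**Working it through.** The protocol gives no power, alpha or expected change for these comparisons, so there is no figure of its own to reproduce. What can be checked is how much of the pre-post span the course occupies.

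**Inputs**
- Course length: 8 weeks (Synopsis, Section 5.2).
- Wait from referral to first session: 10 weeks on average in the group's earlier study (Section 1.2); up to 6 months, about 26 weeks, on the usual waitlist (Section 4.1.1). Both describe usual care. The wait of trial patients is not given.
- Final-survey window: 1 week (Sections 5.2, 5.3.3) or 2 weeks (Section 4.1.1).
- Assumption: the course starts directly after the first therapist visit, and the final visit follows directly after the course.

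**Formulas**
- Span = wait + 8 + (1 or 2) weeks.
- Course share = 8 / span.

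| Wait (weeks) | Span (weeks) | Course share |
|---|---|---|
| 0 | 9-10 | 8/10 = 80% to 8/9 = 89% |
| 4 (assumption) | 13-14 | 8/14 = 57% to 8/13 = 62% |
| 10 (usual-care average) | 19-20 | 8/20 = 40% to 8/19 = 42% |
| 26 (usual-care upper end) | 35-36 | 8/36 = 22% to 8/35 = 23% |

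The zero-wait row is also what results if the baseline moves to the first therapist visit and the final-survey window stays as it is.

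**What a shift would do to the test (illustration only).** Suppose the videos have no effect and other causes move the mean change by d standard deviations of change. With a two-sided 5% level (assumed), the rejection probability comes from the noncentral t distribution with n - 1 degrees of freedom and noncentrality d × √n. For d = 0.2, 0.3 and 0.5 (assumed) it is 0.09, 0.14 and 0.29 at n = 10, and 0.14, 0.25 and 0.57 at n = 20. The documents give neither the size nor the sign of d.

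**Precision of a drift estimate from the same patients.** The 95% half-width is t / √n in standard deviations of change. For SF-12 with all 20 patients it is 2.093/√20 = 0.47. Each patient completes only one of four symptom instruments (Section 4.2.2). With 20 patients split evenly (assumption), 5 per instrument gives 2.776/√5 = 1.24.

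**The case against.** The strongest reply is that the 10-week and 6-month figures describe usual care, and the 6-month waitlist is the very reason Section 4.1.1 gives for moving trial patients forward. The actual gap may be short. That stands: the 40-42% and 22-23% shares are scenarios, not forecasts. But giving a visit priority is not the same as setting a window, and nothing in the protocol limits the gap or takes a fresh baseline.

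A second reply is that time shares do not measure bias. That also stands. A reader might infer that improvement is to be expected even if the videos do nothing. The documents do not support this. They report no drift, symptoms may worsen while patients wait (Section 2.3.1 itself mentions persistent or worsening dysfunction), and worsening would hide a benefit. Nor can a size be given for regression to the mean: entry requires a diagnosis with referral (Section 4.3.2), not a score above a cut-off, and no test-retest correlation or selection distance is stated.

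A third reply is that the in-person sessions belong to the package, which Section 1.1 describes as hybrid. This weakens any complaint about the final session lying before the final survey, although Sections 3.1, 3.3 and 5.1.1 attribute the change to the video-based programme. The first session stays inside the interval under either schedule.

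Finally, this is a feasibility pilot and the surveys are secondary. That limits the stakes; it does not justify leaving the baseline loose when aligning it is so cheap.

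**Conclusion.** The point holds in a limited form. The plan's baseline for SF-12 and the symptom scores has no fixed relation to the start of the course, and the change it calls efficacy includes a pre-course wait with no upper limit. Depending on that unknown wait, the 8-week course would fill 80-89% of the interval (no wait), 40-42% (10 weeks) or 22-23% (26 weeks), given that course and visits follow each other without further gaps. The size and direction of any resulting distortion cannot be stated from the documents. Only the secondary outcomes are affected. It is worth correcting before enrolment goes further, but it does not threaten the feasibility aims.

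**What to change.** 1. Repeat the SF-12 and the patient's assigned symptom survey at the start of the first therapist visit, and define these as the baseline in the paired analysis (Sections 5.1, 5.2, 5.3.3, 5.4.1).
2. Keep the referral survey and report the referral-to-first-visit change descriptively, together with the length of that interval. State that it is imprecise with 10-20 patients and one of four symptom instruments each, and that it should not be used to correct the course-period change.
3. Give the final SF-12 and symptom surveys before the final in-person session, and reconcile the 1-week and 2-week windows in the same edit.
4. In Section 5.1.1, describe the change as exploratory instead of as efficacy. Moving the baseline takes out the waiting time, but without a control group some regression to the mean and natural change remain, and the first in-person session is still inside the interval.

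The cost is one extra survey of 5-10 minutes per patient at a visit that already takes place, a change of order at the last visit, and slightly more survey burden. No new visit is needed.
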